Radiographic appearance (anteroposterior and lateral X-ray at one year): heterotopic ossification will be classified according the classification scheme of Broberg and Morrey as a bone exostosis or as a soft tissue ossification of a ligament, capsule or muscle ("myositis ossificans") [23]; degenerative changes will be classified as grade zero (no change), grade 1 (slight narrowing of the joint space with small osteophytes), grade 2 (moderate narrowing of the joint space, osteophytes and subchondral sclerosis), and grade 3 (severe narrowing of the joint space, large osteophytes, subchondral sclerosis and cystic deformation).

The incremental cost-effectiveness ratio of functional versus plaster treatment will be expressed in a cost-utility ratio, i.e., in terms of cost per QALY. The economic evaluation will be performed from a societal perspective, and will include both health care costs and costs of production losses. Health care costs will include costs of general practice care, medical specialist care, physical therapy, hospitalization, medication, and other costs directly associated with diagnosis, treatment and rehabilitation. Patients will be asked to administer a custom-made questionnaire to register their health care needs and production loss.

In addition to the outcome variables mentioned above, the following data will be collected:

a) Intrinsic variables (baseline data): age, gender, American Society of Anesthesiologists' ASA classification, tobacco consumption, alcohol consumption, comorbidity, social status/household composition, dominant side, and medication use.

b) Injury related variables: affected side, mechanism of injury, and assessment of varus, valgus and posterolateral rotatory instability.

c) Intervention-related variables: reduction delay (i.e., time between dislocation and reduction), time between injury and start of physical therapy, days of sling use, and number of physical therapy sessions

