### Study procedures [Table 1]

**Table 1 T1:** Schedule of events

	Screening	Enrollment	Baseline	1 week	3 weeks	6 weeks	3 months	6 months	12 months
				(3-10 d)	(11-28 d)	(4-8 we)	(11-15 we)	(5-7 mo)	(12-14 mo)
**Screening**	X								

**X-ray**	X		X (<24 h post-reduction)	X					X

**Informed Consent**		X							

**Randomization**		X							

**Baseline data**			X						

**Clinical follow-up**				X	X	X	X	X	X

**Revisision surgery**				X	X	X	X	X	X

**Complications**				X	X	X	X	X	X

**Pain (VAS)**				X	X	X	X	X	X

***Quick-*DASH**						X	X	X	X

**MEPI**						X	X	X	X

**Oxford Elbow Score**						X	X	X	X

**SF-36**						X	X	X	X

**EQ-5D**						X	X	X	X

**Health care consumption**						X	X	X	X

**ROM**						X	X	X	X

**Early withdrawal**				*	*	*	*	*	*

*, only if applicable

Clinical assessments will occur at the time of admission (baseline), one week (3-10-day window), three weeks (11-28-day window), six weeks (4-8-week window), three months (11-15-week window), six months (5-7-month window), and 12 months (12-14-month window) after start of treatment.

At each FU visit, the research coordinator or research assistant will ascertain patient status (i.e., secondary interventions, adverse events/complications, deaths) and will verify information within medical records.

At each FU visit, the patients will be asked to indicate the pain level on a VAS.

At each visit from six weeks onwards, the ROM of the elbow will be measured using a goniometer by a doctor blinded for the treatment of the dislocation. This will be used to calculate the MEPI index. In addition, patients will be asked to complete the questionnaires relating to disability (*Quick-*DASH score including optional modules, Oxford Elbow Score), health-related quality of life (SF-36, EQ-5D), and healthcare consumption.

Plain X-rays of the elbow will be made at the time of presentation in the hospital (baseline), post-reduction, and at the follow-up visit after one week and one year. The X-ray at 12 months will be taken in order to determine the amount and location of heterotopic ossification and the grade of degenerative joint changes. This is common practice in this type of patient. At the last visit, the surgeon will document any surgery that may be planned for the patient.

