### Statistical analysis

Data will be analyzed using the PASW Statistics version 18.0.1 or higher (SPSS, Chicago, Illinois, USA). Normality of continuous data will be tested with the Shapiro-Wilk and Kolmogorov-Smirnov test and by inspecting the frequency distributions (histograms). The homogeneity of variances will be tested using the Levene's test.

The analysis will be performed on an intention to treat basis. Patients with protocol violations will be followed up, and data will be recorded. Data will be analyzed with and without inclusion of patients with protocol violation.

Descriptive analysis will be performed to report baseline characteristics (intrinsic variables and injury-related variables) in both treatment groups. For continuous data (e.g., age, Quick-DASH score at baseline) mean ± SD (parametric data) or medians and percentiles (non-parametric data) will be calculated. For categorical data (e.g., gender, ASA grade, alcohol and tobacco consumption, dominant and affected side) frequencies will be calculated.

The mean difference between the mean *Quick-*DASH scores of the functional group and the plaster group will be tested. Univariate analysis will be performed to test the difference in the primary and secondary outcome measures between the functional and the plaster groups. Continuous data will be tested using a Student's T-test (parametric data) or a Mann Whitney *U*-test (non-parametric data). Chi-square analysis will be used for statistical testing of categorical data. A p-value <0.05 will be taken as the threshold of statistical significance.

A multivariable linear regression analysis will be performed to model the relationship between different covariates and the *Quick-*DASH score. Intrinsic and injury-related variables that display a p-value <0.5 in the univariate analyses will be added as a covariate.

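### The regression picks its covariates at p<0.5 from the trial's own data and does not name treatment as a term, and the baseline Quick-DASH listed for summary is never collected

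*Protocol article*

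**What the plan says.** All of this is in the protocol article.

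- **Purpose of the regression (Statistical analysis).** "A multivariable linear regression analysis will be performed to model the relationship between different covariates and the" Quick-DASH score. Treatment group is not mentioned as a term.
- **Choice of covariates (same section).** "Intrinsic and injury-related variables that display a p-value <0.5 in the univariate analyses will be added as a covariate".
- **Univariate analysis (same section).** The only one described is a comparison of the arms: "Univariate analysis will be performed to test the difference in the primary and secondary outcome measures between the functional and the plaster groups". No screen of covariates against Quick-DASH is described.
- **Candidates (Outcome measures, additional data).** Nine intrinsic variables are listed. The injury-related variables are affected side, mechanism of injury and "assessment of varus, valgus and posterolateral rotatory instability". Quick-DASH is in neither list.
- **Baseline summary (Statistical analysis).** The examples are introduced with "For continuous data (e.g., age, Quick-DASH score at baseline".
- **Schedule (Study procedures, Table 1).** Quick-DASH is marked at 6 weeks and at 3, 6 and 12 months only. The text agrees: "At each visit from six weeks onwards, the ROM of the elbow will be measured using a goniometer", and then "In addition, patients will be asked to complete the questionnaires relating to disability".

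**The concern.** A covariate rule in a protocol should let two analysts arrive at the same model, and the model should answer a question the trial asks. This rule does neither.

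Which covariates enter depends on the data, at a threshold that screens out only half of the irrelevant ones. The wording does not settle what each variable is tested against. If it is Quick-DASH, the p-values later shown for the selected covariates ignore the selection and are too small. If it is treatment arm, the rule selects on chance imbalance after randomisation.

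The primary objective is a comparison of arms, yet the regression is described only as relating covariates to Quick-DASH. As written it defines no adjusted treatment difference.

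Separately, a baseline summary of the primary outcome measure is announced for which no data will exist. At stake are the reproducibility and interpretation of a supporting analysis and one line of the baseline table.

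**Working it through.** **Inputs**

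- Candidates: 9 intrinsic variables, plus 3 injury-related items, or 5 if the three instability tests count separately. Total 9 + 3 = 12 to 9 + 5 = 14.
- Patients: the Sample size calculation section gives 41 per group, so 2 × 41 = 82 evaluable. That 41 reproduces with a t-based calculation (difference 7.5, SDs 15 and 7.5, power 80.8%); the normal approximation gives 40. It serves here only to set n.
- Thresholds: p<0.5 to enter; p<0.05 for significance.

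The plan gives no figure for the regression itself, so there is none to reproduce.

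**Step 1: how many unrelated covariates enter.** A variable with no association has a uniform p-value, so the expected number entering is k × 0.5.

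| Candidates k | Expected at p<0.5 | P(at least 5 enter) | Expected at p<0.05 |
|---|---|---|---|
| 12 | 6.0 | 81% | 0.6 |
| 14 | 7.0 | 91% | 0.7 |

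**Step 2: what selection does to the covariate p-values, if the screen is against outcome.** For an unrelated variable, P(p<0.05 given p<0.5) = 0.05/0.5 = 10%. This is exact for the univariate p-value. Simulation of the multivariable model (82 patients, 14 independent null covariates, treatment included) also gives about 10% of entered covariates at p<0.05. With all 14 fixed in advance it is the nominal 5%. A screen against arm does not use the outcome and so does not shrink these p-values in this way.

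**Step 3: effect on the treatment test, if treatment is in the model.**

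- Type I error: 4.7% to 5.2% in simulations with 80 completers and 12 or 14 candidates, and 5.2% in a run with 82 patients.
- Spread of the treatment estimate, no covariate mattering: SD 0.222 with the rule, 0.221 unadjusted.
- Spread with one covariate explaining 20% of variance (assumed): 0.200 with the rule, 0.198 with that covariate alone fixed. 0.200/0.198 = 1.01, a difference of about 1%.

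**Step 4: baseline Quick-DASH, section against section.** The Statistical analysis section describes baseline characteristics as intrinsic and injury-related variables and gives a baseline Quick-DASH as an example. The lists of those variables do not contain it, and Table 1 first marks it at six weeks. The summary cannot be produced from the scheduled data.

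**The case against.** The strongest reply is that little of consequence depends on this regression. Quick-DASH is compared between arms by a t-test or Mann-Whitney test, and the regression is additional. That stands: the primary unadjusted test is untouched.

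A reader might infer stronger harms, which the documents and the checks do not support:

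- **Inflated error for the treatment comparison.** Step 3 shows otherwise.
- **The rule causes a high chance of at least one false predictor.** With 14 null covariates, about 49% of trials show at least one at p<0.05 (48.6% in simulation with the screen), but the figure is 48.0% with all 14 fixed in advance. This is ordinary multiplicity: 1 − 0.95^14 = 51%. The screen is not its source.
- **Important prognostic factors are left out.** A lenient threshold seldom does this. At 82 patients a covariate explaining 10% of variance is dropped in about 1% of trials. The article names no established prognostic factor.
- **A fixed list would be materially more precise.** Covariates explaining 10% to 20% of variance would cut the standard error by 5% to 11% (√0.9 = 0.949, √0.8 = 0.894), but that compares adjusted with unadjusted analysis. The p<0.5 rule captures nearly all of that gain.
- **Treatment is excluded from the model.** The text does not say so. Adding a covariate could mean adding it to a model that already holds treatment. What can be said is that the stated purpose does not include treatment.
- **Baseline Quick-DASH is a regression covariate.** It appears only as an example in the descriptive paragraph, and no change-from-baseline analysis is planned.

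It may also be said that a short article leaves model detail to the full protocol or analysis plan. That would excuse silence. Here the article states a selection rule and a model purpose, and it contradicts its own schedule. If 0.5 is a misprint for a smaller value, it still needs correcting, and selection from the trial's data would remain.

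**Conclusion.** The point holds as a defect in a supporting analysis and a contradiction about one baseline item.

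- The p<0.5 rule would admit on average 6 to 7 of 12 to 14 unrelated candidates, about ten times as many as p<0.05.
- If the screen is against outcome, unrelated covariates that enter reach p<0.05 about 10% of the time instead of 5%. The article does not fix whether the screen is against outcome or arm, so this figure is conditional.
- No adjusted treatment difference is defined, because treatment is not stated to be in the model.
- The baseline Quick-DASH has no data source.

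The primary comparison is not threatened, and neither the size nor the precision of a treatment test in such a model is materially harmed. The figures assume independent covariates, each entered as a single term, with none related to outcome in the null case, and 80 to 82 evaluable patients. The count of 12 to 14 depends on how the instability tests are counted.

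**What to change.** 1. Replace the p<0.5 rule with a linear model for Quick-DASH containing treatment arm and a short list of covariates fixed in advance from the intrinsic and injury-related variables already listed under Outcome measures (for example age, gender, whether the dominant side is affected, and instability at injury). Report the adjusted treatment difference with its 95% confidence interval, in addition to the planned unadjusted test.
2. Delete the baseline Quick-DASH example from the Statistical analysis section. Deletion is simpler than adding the form: recruitment began on August 26, 2009, so a questionnaire added now would miss patients already enrolled.

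Both changes are to wording and need no new data. The downside of the first is that the investigators must commit to the list before seeing the data and cannot later swap in a variable that turns out to be associated with outcome.

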### Ethical considerations

The study will be conducted according to the principles of the Declaration of Helsinki (59th World Medical Association General Assembly, Seoul, October 2008) and in accordance with the Medical Research Involving Human Subjects Act (WMO).

The Medical Ethics Committee Erasmus MC (Rotterdam, The Netherlands) acts as central ethics committee for this trial (reference number MEC-2009-239; NL28124.078.09). Approval has been obtained from the local Medical Ethics Committees in all participating centers. An information letter notifying the patients' participation will be sent to their general practitioners, unless a patient does not agree with this.

The Medical Ethics Committee Erasmus MC has given dispensation from the statutory obligation to provide insurance for subjects participating in medical research (article 7, subsection 6 of the WMO and Medical Research (Human Subjects) Compulsory Insurance Decree of 23 June 2003). The reason for this dispensation is that participation in this study is without risks.

## Discussion

The FuncSiE trial will compare management of simple elbow dislocations by early functional treatment with treatment by plaster immobilization. Early functional treatment may lead to a better ROM and prevent elbow stiffness. To date no RCT for the management of simple elbow dislocation has been performed with a sample size of 100 patients. Inclusion of patients has been started August 26, 2009 and the expectation is to include 8 patients per month. With a follow-up of one year the presentation of data will be expected in the beginning of 2012.

## Abbreviations

ASA: American Society of Anesthesiologists; BP: Bodily Pain; CONSORT: CONsolidated Standards of Reporting Trial; DASH: Disabilities of the Arm: Shoulder and Hand score; ED: Emergency Department; EQ-5D: EuroQol-5D; GH: General Health perception; HR-QoL: Health-related Quality of Life; MCS: Mental Component Scale; MEPI: Mayo Elbow Performance Index; MH: general Mental Health; NTR: Netherlands Trial Registry (in Dutch: Nederlands Trial Register); PCS: Physical Component Scale; PF: physical functioning; QALY: Quality-Adjusted Life Years; QoL: Quality of Life; RCT: Randomized Controlled Trial; RE: Role limitations due to Emotional problems; ROM: Range Of Motion; RP: role limitations due to physical health; SF: Social Functioning; SF-36: Short Form 36; SPSS: Statistical Package for the Social Sciences; VAS: Visual Analog Scale; VT: vitality, energy, or fatigue.

